## Material and methods

### Research design

A two-arm, parallel-group, randomized controlled trial (RCT) will be carried out to determine the effectiveness of the iABCT on improving the quality of life and well-being of a chronic medical illness population by comparing individuals who have access to the intervention with a WL control group.

Participants will be randomly assigned to one of the two conditions: a) intervention group, and b) control group (WL) and will complete different measures at different assessment points: baseline time (pre-assessment), and 3- and 6-month follow-up. Participants of the WL group will receive access to the iABCT once they fulfill the 3-month assessment.

### Study setting and recruitment

Participants will be recruited from April 2021 to April 2022 by several means, including the study website and flyers posted on social media platforms (e.g., Facebook, Instagram, LinkedIn), doctors’ referrals, and through chronic illness patients’ associations. All distributed materials will include a dedicated email address through which participants could contact the research team for further information on the study.

### Eligibility criteria

Participants will be selected according to the following eligibility criteria:

#### Inclusion criteria

(1) Age > 18 years; (2) ability to understand and read Spanish; (3) access to a computer with the Internet; and (4) diagnosis of one of the following chronic medical conditions: diabetes, inflammatory bowel disease, fibromyalgia, low-back chronic pain, migraines and other conditions.

#### Exclusion criteria

(1) Terminal disease; (2) severe psychiatric disorders comorbidities (schizophrenia, substance dependence, bipolar disorder, psychotic illness) or severe neurologic or medical condition; and (3) receiving psychological treatment or mindfulness training at the time of recruitment.

### Intervention

#### Experimental group. Internet attachment-based compassion therapy (iABCT)

The iABCT is an online self-applied version of Attachment-based Compassion Therapy (ABCT) that has been adapted and optimized to be delivered via the Internet [42]. As mentioned, the ABCT is based on the attachment theory and the use of compassion meditations, and therefore includes practices to raise awareness and/or address maladaptive aspects (when appropriate) of attachment styles developed with parents and compassion and self-compassion practices to improve interpersonal relationships and well-being general [31]. Following the original version, the iABCT is composed of 8 modules that have been formulated to be completely self-applied and share the same structure: (1) module objectives; (2) theoretical contents of the module; (3) exercises and activities (including formal and informal practices) to put what is learned in the module into practice; (4) assessment of the knowledge acquired during the module; (5) tasks to be completed before advancing to the next module (homework assignments); and (6) summary of the module. Formal and informal compassion and self-compassion meditations such as receiving and giving compassion to oneself, friends, unknown people, and people deemed to be problematic; identifying their own attachment style; and understanding how it influences their current interpersonal relationships, are practiced during the intervention. The content of the modules includes texts, images, illustrations, videos, audio-guided meditations, interactive exercises, and daily homework assignments. Downloaded PDF files will be made available so that users can review them offline. Each module has been optimized to have a duration of approximately 60 or 90 minutes. The entire intervention is estimated to be completed in eight weeks. For more information about the iABCT, see Refs [42].

#### Control group. Waiting list (WL) control group

The control group will receive no intervention for the first three months after enrolling in the study and complete the first assessment (pre-assessment). After completing the second assessment (3 months), participants in this condition will be informed that they will have access to the iABCT program.

### Strategies for monitoring and improving intervention protocol adherence

In order to improve adherence, email reminders will be sent after 7 days if participants have not started with the pre-assessment (for both groups) or the treatment modules (for the intervention group) yet. These reminders will contain messages encouraging them to start with the assessment or intervention (in the case of the intervention group) and asking them for any difficulties or technical problems to enter the web platform. Moreover, an email at the midpoint of the intervention (module 3) will be sent to those participants who have not progressed through the intervention. In this case, messages will include positive reinforcement to the participants, reminders of the importance of reviewing the modules and encouraging messages to do the homework tasks and continue with the iABCT program.

### Data collection and outcomes

Participants will be assessed at baseline (pre-assessment) and 3- and 6-month follow-up.

Assessments will be conducted online via the platform web (https://psicologiaytecnologia.labpsitec.es/), where the iABCT is hosted. Outcome assessment will follow the schedule outlined in Fig 1.

**Fig 1 pone.0278462.g001:**
[figure not shown]
SPIRIT flow diagram: Schedule of enrolment, interventions and assessments.

#### Screening related measures

*Sociodemographic variables and meditation practice*. To ensure that eligibility criteria are met, information regarding diagnosis of any mental or physical condition will be collected and participants will be asked if they are receiving a psychological intervention or a training based on the practice of meditation prior to being enrolled in the study.

Demographic data (age, sex, nationality, educational level, occupation, and civil status) will be collected as part of the baseline assessment (pre-assessment). Variables regarding overall meditation practice will be recorded as follows: any or no meditation experience, source of learning (i.e., self-taught, therapy context, teacher or secular training course, and religious context), frequency of meditation (daily, 3 or 4 times a week, once a week or less, 2 or 3 times per month, sporadically, never), duration of each session (mean time in minutes), and lifetime practice (in years), and for participants with experience, the amount of time (in months) of meditation practice interruption and context of practice (secular or religious).

#### Primary outcome measure

*Quality of life*. The EuroQol 5-Dimensions Questionnaire (EQ-5D; [43]) is a self-report measure that assesses the health-related quality of life (HRQOL) using five dimensions of functionality in daily-life: mobility, self-care, usual activities, pain/discomfort and anxiety/depression. and three levels of severity. Responses in each dimension are divided into three levels of severity: (1) no problems; (2) moderate problems; and (3) extreme problems. Moreover, the EQ-5D includes a visual analogue scale (EQ VAS) in which participants self-rate their quality of life in a range from 0 (worst imaginable health state) to 100 (best imaginable health state). The Spanish version of this scale has shown good reliability and validity properties [44].

*Well-being*. The Pemberton Happiness Index (PHI; [45]) is a scale which includes 11 items related to different domains of remembered well-being (general, hedonic, eudaimonic, and social well-being) and ten items related to experienced well-being (i.e., positive and negative emotional events that possibly happened the day before); the sum of these items produces a combined well-being index that ranges from 0 to 10. Results from the Spanish validation study provided very good support for the psychometric properties of the PHI (α = .92) ([45]).

#### Secondary outcome measures

*Compassion and self-compassion*. The Sussex-Oxford Compassion for the Self Scale (SOCS-S; [46]) is a 20-item scale that assesses the levels of self-compassion in a 5-point Likert scale ranging from 1 (not at all true) to 5 (always true). It includes 5 subscales: recognizing suffering, understanding the universality of suffering, feeling for the person suffering, tolerating uncomfortable feelings, and acting or being motivated to act to alleviate suffering. The validation study of this scale has shown adequate psychometric properties (Cronbach’s alphas ranged from .75 to .93 for total SOCS-S scale and subscale items) [46]. For this study a translated and adapted version of the original scale into Spanish will be used.

*Self-care behaviors*. The Mindful Self-Care Scale—Brief version (B-MSC; [47]) is the 24-item shortened version of the Mindful Self Care Scale (MSCS; [48]). This scale measures the frequency of self-care behaviors addressed in 6 domains: mindful relaxation, physical care, self-compassion and purpose, supportive relationships, supportive structure, and mindfulness. Cronbach’s alpha for the B-MSCS domains showed adequate values ranging from .74 to .86 [47]. In this study, a translated and adapted version of the original scale into Spanish will be used.

*Specific illness interference measures*. Specific questionnaires will be used to assess specific illness interferences for the different medical conditions included in the study: the Diabetes Distress Scale (DDS; [49]) for participants with type I and type II diabetes; the Roland-Morris Questionnaire [50] for participants with low-back chronic pain; the Revised Fibromyalgia Impact Questionnaire (FIQR; [51]) for participants with fibromyalgia; the Migraine Disability Assessment questionnaire (MIDAS; [52]) for participants with migraines; and the Inflammatory Bowel Disease Questionnaire (IBDQ-32; [53]) for participants with inflammatory bowel illness.

*Self-criticism*. The Self-critical Rumination Scale (SCRS; [54]) is a 10-item questionnaire measuring self-criticism, defined as a form of negative thinking that devalues the self. It assesses thoughts that criticize the self for perceived errors, failures, weaknesses, defects, bad habits, or general inadequacy. It takes into account the ruminative qualities of thought: frequency, duration, repetition, and difficulty of control. Final scores range from 10 to 40 and higher scores indicate a higher level of self-criticism. The Spanish validation of this scale has shown good psychometric properties (α = .91) [55].

*Symptomatology*. The Depression, Anxiety and Stress Scale (DASS-21; [56]) is an abbreviated form of the DASS questionnaire containing 21 items and organized in three subscales to assess anxiety, depression, and stress symptomatology. Responses indicate the presence of each symptom over the past week on a 4-point Likert-type scale ranging from 0 (*never*) to 3 (*almost always*). The Spanish validation of this scale has shown acceptable internal consistency (Cronbach’s alpha for the total score was 0.94 and Cronbach’ alpha for Depression, Anxiety and Stress scales were 0.85, 0.85 and 0.87, respectively) [57].

*Attachment styles*. The Relationships Questionnaire (RQ; [58]) uses a 7-point Likert-scale that assesses and matches participants with one of four attachment styles: (i) secure, (ii) preoccupied, (iii) dismissive and (iv) fearful. Studies for both original and Spanish versions of the scale have demonstrated that the reliability of the self-descriptor criteria is high [59].

*Social support*. The Medical Outcomes Study-Social Support Survey (MOS-SSS; [60]) is a 20-item questionnaire that analyzes the perception of social support. Item 1 refers to the size of the social network and the remaining 19 items measure four dimensions of functional social support: emotional (8 items), instrumental (4 items), positive social interaction (4 items), and affective support (3 items). The items present a 5-point response scale that measures progressively (from never to always) how often each type of social support is available to the caregiver. A total score can also be obtained, where higher scores would indicate more support received. The Spanish version of the scale has shown good reliability properties (α = .94) [61].

*Illness perception*. The Illness Perception Questionnaire-Revised (IPQ-R; [62]) was designed to assess the cognitive and emotional dimensions of illness representations. The IPQ-R consists of three sections. Two scales measure the identity and causal dimensions, and another general section assesses the dimensions of duration (acute/chronic), cyclical course, consequences, personal control, treatment control, coherence, and emotional representations. Cronbach’s alpha values in the Spanish validation study showed acceptable psychometric properties, ranging from .39 to .81 for the different subscales [63].

*Difficulties in compassion meditation practice*. The Compassion Practice Quality Scale (CPQS) [64] has been developed to assess the key aspects of compassion practices (e.g., mental imagery, sense of connection and warmth, compassionate phrases, and compassionate gestures). This self-reported questionnaire includes two subscales (imaginery and somatic perception) with a total of 10 items that participants score on a scale ranging from 0 to 100 indicating the percentage of the time that their experience reflects each statement. Higher scores indicate higher quality of practice (i.e., less practice difficulties). Both subscales (imagenery and somatic) have been shown to be reliable, with Cronbach’s alpha values of .90 and .88 respectively [64].

#### Acceptability outcome measures of intervention

*Expectations and satisfaction*. Expectancy and satisfaction questionnaire (adapted by Campos et al., 2020 [42] from Borkovec and Nau, 1972 [65]). These questionnaires were adapted from Borkovec and Nau (1972) [65] to measure participant expectations before the intervention and their later satisfaction with it. Each scale includes six items rated from 0 ("not at all") to 10 ("very much"). The questions addressed how logical the intervention seemed, to what extent the participant expected to be satisfied with it, whether the participant would recommend the intervention to others, whether it would be useful for psychological problems, the interventions’ usefulness for the participants, and to what extent it could be aversive (reverse item). Higher scores represent higher expectations and satisfaction levels.

*Usability*. System Usability Scale (SUS; adapted by Campos et al., 2020 [42]). This instrument was adapted from the System Usability Scale (SUS) in order to assess the usability of a service or product and the acceptance of technology by the people who use it. The SUS has been shown to be a valuable and robust tool for assessing the quality of a wide range of user interfaces, as it is easy to use and understand. This scale includes 10 statements rated on a five-point scale measuring agreement with the statement (0 = strongly disagree; 4 = strongly agree). The final score is obtained by adding the scores on each item and multiplying the result by 2.5. Scores range from 0 to 100, where higher scores indicate better usability.

*Participant’s opinion*. ***Semi-structured qualitative interview*.** A qualitative interview will be adapted to explore reasons for participant’s dropout or no participation in the trial [66, 67]. Reasons for dropping out or not participating in the trial will be further explored using an online form with pre-set response options, and multiple reasons will be allowed. Additionally, options will be available to expand participants’ qualitative responses. A final three open questions will explore the general opinion of the program.

### Participant timeline

Interested participants will receive an access link to fill in the written informed consent together with the screening questionnaire through the LimeSurvey platform (https://www.limesurvey.org/es/). The eligibility assessment will consist of demographic questions, assessment of history and current state of mental health and treatment history, and type or chronic medical illness diagnosis. After consenting, eligible participants will be identified with a code to which only the researcher will have access. They will then be registered on the Psychology and Technology web platform (https://psicologiaytecnologia.labpsitec.es/) to complete the assessment measures at different points in time: pre-assessment and follow-up assessments. Participants in the intervention condition will receive an email after intervention completion to get their feedback on the program (e.g., ease of use, barriers, possible improvements).

Participants in the WL group will be able to access the web platform for the intervention at 3 months (after the active treatment group).

### Sample size

The sample will be composed of 68 participants as minimum. The sample size was calculated using the G*Power 3.1.9.7 for Windows program [68]. Estimated sample size was decided based on medium effect sizes (d = 0.4), statistical power of .80 and α = .05, indicating a necessary sample of 52 participants [69]. Considering that the dropout rate in Internet-based interventions for the chronic medical ill population is usually around 30%, a target of 34 people per group was set [70–72].

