We hypothesize that: (a) iABCT condition will be more efficacious than the WL group in improving quality of life and well-being and other secondary variables at 3-month follow-up; (b) the gains achieved after iABCT will be maintained at 6-month follow-up; and (c) the iACBT will be well accepted in terms of expectations, satisfaction, usability and opinion by the participants; (d) participants in WL group will show an improving quality of life and well-being and other secondary variables at a 6-month follow-up, once they receive the iABCT; (e) improvements in quality of life and well-being scores will be predicted by self-reported self-compassion and secure attachment; (f) frequency of meditation practice will moderate the improvement in quality of life and well-being after receiving the iABCT; and (g) changes in compassion, self-criticism and attachment style will appear as mediators of greatest changes in quality of life and well-being. Regarding objective 7, no specific hypotheses are proposed due to the exploratory nature of the qualitative analyses.

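### The 52 participants stated for d = 0.4 and 80% power do not fit the iABCT versus waiting-list comparison at 3 months, which needs about 100 analysed per arm

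*Protocol article*

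**What the plan says.** The Sample size section of the protocol article names the software ("The sample size was calculated using the G*Power 3.1.9.7 for Windows program") and the inputs and result: "medium effect sizes (d = 0.4), statistical power of .80 and α = .05, indicating a necessary sample of 52 participants". It then allows for dropout of about 30%, and "a target of 34 people per group was set", which gives the minimum of 68. It does not state the test, the sidedness, the number of measurements or a correlation between them.

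The main hypothesis, (a) in the Objectives section, is between arms: "iABCT condition will be more efficacious than the WL group in improving quality of life and well-being and other secondary variables at 3-month follow-up". Allocation is 1:1 (Allocation and blinding). Waiting-list participants get access to the programme once they have completed the 3-month assessment (Research design), so 3 months is the last visit with an untreated control. Statistical methods plans a linear mixed model with a random intercept, group as a between-group factor, and time (baseline, 3 and 6 months) as a within-group factor. It also plans between-group Cohen's d with a 95% CI.

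**The concern.** A total of 52 is far too small for a two-group comparison at a standardised difference of 0.4. If d = 0.4 is the difference between iABCT and waiting list, the article claims a power that its design does not have. The paragraph is the article's only justification of the sample size. A reader of a non-significant 3-month result could take it that an effect of 0.4 had been tested with 80% power when the real chance of detecting it was much lower.

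**Working it through.** **Inputs.** From the Sample size section: d = 0.4, power 0.80, α = 0.05, N = 52, dropout 30%, target 34 per group. The 52 must be a total, because 52 × 1.3 = 67.6, rounded up to 68 = 2 × 34. At 1:1 that is 26 per arm. Sidedness is not stated; two-sided is taken as the main case. The baseline to 3-month correlation r is not stated; 0.5 to 0.7 is assumed, with 0.8 for illustration. Power is from the noncentral t or F distribution.

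**Step 1. Which calculations return 52?** Two standard ones do.
- Paired (one-sample) t-test, two-sided, d = 0.4: noncentrality d√n = 0.4 × √52 = 2.88 on 51 df gives power 0.808. With n = 51 it is 0.7999, so 52 is the smallest n.
- Repeated-measures 2 × 2 interaction (two groups, two measurements) with f = 0.2 and r = 0.5: λ = f² × N × m / (1 − r) = 0.04 × 52 × 2 / 0.5 = 8.32 gives power 0.807. With N = 50 it is 0.791.

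The first is a within-person effect with no control arm. In the second, if the arms are equal at baseline and differ by d at follow-up, each cell's interaction term is ±d/4, so f = d/4. Then f = 0.2 means a between-arm difference of 0.8 SD, and d = 0.4 means f = 0.1.

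**Step 2. What does the between-arm comparison need?** For a two-sample t-test the noncentrality is d√(n/2), with n per arm.
- Two-sided: n = 100 gives 0.4 × √50 = 2.83 and power 0.804; n = 99 gives 0.7997. Requirement: 100 per arm, 200 in total.
- One-sided: 78 per arm, 156 in total.
- The 2 × 2 interaction with f = 0.1 and r = 0.5 also needs N = 200.

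**Step 3. Power at d = 0.4 with 26 per arm.** The noncentrality is 0.4 × √13 = 1.44, giving 29.3% two-sided (41% one-sided). The interaction with f = 0.1, r = 0.5 and N = 52 gives the same 29.3%.

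Using the baseline changes the effective d. A change contrast divides it by √(2(1 − r)); entering baseline as a covariate (ANCOVA) divides it by √(1 − r²). Two-sided power at 26 per arm:

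| Assumed r | Change contrast | Baseline as covariate |
|---|---|---|
| 0.5 | 29% | 37% |
| 0.6 | 35% | 42% |
| 0.7 | 45% | 51% |
| 0.8 | 61% | 65% |

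Power of 80% is reached only at r of about 0.87 (change) or 0.86 (covariate).

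The planned model has baseline as a level of the time factor, so the change column is the relevant one for its baseline to 3-month contrast.

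**Step 4. Completers.** 68 × 0.7 = 47.6, about 24 per arm, where unadjusted power is 27%. To retain 52 after 30% loss would take 52 / 0.7 = 74.3, rounded up to 75. With no loss at all (34 per arm), unadjusted power is 37%.

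**Step 5. Effect detectable with 80% power, two-sided.**

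| Analysed per arm | Unadjusted, or change at r = 0.5 | Change at r = 0.6 | Covariate at r = 0.6 |
|---|---|---|---|
| 24 | 0.83 | 0.74 | 0.66 |
| 26 | 0.79 | 0.71 | 0.63 |
| 34 | 0.69 | 0.62 | 0.55 |

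The last two columns are the first multiplied by √0.8 = 0.894 and by √0.64 = 0.8.

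**The case against.** The strongest reply is that the article condenses a fuller calculation. It names no test, and the planned mixed model uses repeated measurements, which can lower the number needed. This stands in part. The 29% holds only for an unadjusted 3-month contrast or for change at r = 0.5, and a higher correlation raises it. It does not rescue the stated figure, because 52 would need r of about 0.86 to 0.87 and the article gives no such value.

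A reader might infer from the exact match in Step 1 that the authors ran a paired test, or entered a wrongly scaled interaction effect. The article does not support that as fact: two different routes give 52, nothing in the text tells them apart, and the source cited for the figure is not available. The finding is that the inputs and 52 do not fit the between-arm comparison, whichever route was used.

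A reader might also quote the more favourable covariate figures (42% power, or a detectable d of 0.63, at r = 0.6) as those of this trial. They do not follow from the plan as written, which does not enter baseline as a covariate.

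Three further points limit the concern. The 68 is a minimum, and the mixed model uses all available observations, so final power is not fixed at the 24- or 26-per-arm value. Nothing in the article says that a null result would be read as evidence against efficacy. The between-group 95% CI is already planned.

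**Conclusion.** The stated power is wrong for the trial's main comparison and should be corrected. With d = 0.4 as a between-arm difference and two-sided α = .05, the requirement is about 200 analysed, against 52 stated. At 26 per arm, power is 29% unadjusted and 29% to 45% for a change contrast at r = 0.5 to 0.7. At the roughly 24 per arm that 68 leaves after 30% loss, it is 27% unadjusted.

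The conclusion rests on two readings: that d = 0.4 is meant as the effect of iABCT against waiting list, as hypothesis (a) requires, and that 52 is a total, as the step to 68 shows. The correlations are assumed. A one-sided test does not change the conclusion (156 in total; 41% power at 26 per arm). How 52 was obtained remains an inference.

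**What to change.** Restate the Sample size section for the between-arm contrast at 3 months, naming the test, the sidedness and the assumed baseline to 3-month correlation.
- Remove the claim of 80% power at d = 0.4.
- Report instead the effect that 68 randomised can detect with 80% power: about d = 0.83 at 24 per arm after 30% loss, 0.79 at 26 and 0.69 at 34, unadjusted or as change at r = 0.5. At 24 to 26 per arm it is about 0.74 to 0.71 for change at r = 0.6.
- Quote the smaller covariate-adjusted figures (about 0.66 to 0.63 at r = 0.6) only if the analysis is changed to adjust for baseline.
- Correct the dropout step, or say that 68 leaves about 24 per arm at 30% loss.
- State that a non-significant 3-month result will be interpreted through the between-group 95% CI already planned.

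The cost is wording and a less favourable stated figure; no extra participants are needed to make the statement correct. If the sponsor prefers to keep 80% power at d = 0.4, that is a separate design decision: about 200 analysed without adjustment, or 200 / 0.7 = 286 randomised at 30% loss.

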### Statistical methods

The latest version of SPSS (v.26) will be used for all data analysis. T-tests for independent-samples (t), ANOVAs, and chi-square analysis (χ2) will be calculated to investigate the characteristics of the randomized sampled and included in the RCT and to explore group differences in participants’ sociodemographic (e.g., age, gender) and clinical data (e.g., quality of life, well-being). Attrition and dropout rates will be calculated by reporting percentages and patterns of missing data. Intent-to-treat mixed-model analyses without any ad hoc imputations will be used to handle missing data in case of participant dropout and to conduct the efficacy analysis [73]. This analysis compares the study groups based on the treatment to which they were randomly allocated. It does not assume that the last measurement is stable, it does not involve any substitution of missing values with supposed or estimated values, it is conducted using all available observations, thus reducing the biases and loss of power caused by the simple deletion or random imputation of incomplete data. Mixed-model analyses are appropriate for RCTs with multiple time points and pre-post designs, and it has showed remarkable robustness to violations of distributional assumptions (e.g., skewed, kurtosis, or heteroscedastic) [74, 75]. To study distributional assumptions and the impact of missing random effect components on model some test will be included: Normality assumptions will be explored using the Shapiro-Wilk test (for each experimental group, N < 50), the Kolmogorov-Smirnov (K-S) test (for the total sample, N > 50), skewness and kurtosis indices, and normality plots (Q-Q plots). Homoscedasticity will be explored by Levene’s test and Box’s M test for equivalence of covariance matrices. Wald statistic (or Z-test) will be conducted to test the residual error variance estimation and the null hypothesis of homogeneity of residuals. The assumption that data is missing completely at random (MCAR) will be evaluated using Little’s MCAR test. it is robust to violations of distributional assumptions. A linear mixed-effect model for each outcome measure will be implemented using the MIXED procedure with one random intercept per subject. An identity covariance structure will be specified to model the covariance structure of the intercept. For each outcome, time (baseline and 3- and 6-month follow-up) will be treated as a within-group factor and group (experimental and control group) as a between-group factor and significance effects will be followed up with pairwise comparisons (adjusted by Bonferroni correction). Cohen’s d effect size and 95% CI will be calculated for within- and between-group comparisons [76, 77]. Sensitivity analyses will be performed to assess the robustness of the findings in terms of different methods for handling missing data (i.e., mixed models with and without imputation, maximum-likelihood estimation, and maximum-likelihood multiple imputation [78]. The means and standard deviations of the acceptability measures of the intervention will be analyzed. For analyses of associations between intervention outcomes, predictors of change and mechanisms of action, several statistical tests such as Pearson’s correlation, multiple regressions and mediation analysis will be performed. In addition, participants’ qualitative responses regarding facilitators and barriers to the intervention will be explored using a qualitative content analysis and coding and categorization approach to the data using word frequency counts with ATLAS.ti software.

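### The target of 68 does not retain the 52 participants the protocol calls necessary: at the expected 30% dropout about 48 remain, 4 to 5 too few.

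*Protocol article*

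**What the plan says.** The Sample size section of the protocol article builds the target in three steps.

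- The design values are "medium effect sizes (d = 0.4), statistical power of .80 and α = .05", "indicating a necessary sample of 52 participants".
- The expected loss follows: "the dropout rate in Internet-based interventions for the chronic medical ill population is usually around 30" per cent.
- The target is tied to that loss in the same sentence: "usually around 30%, a target of 34 people per group was set". The section opens with the total: "The sample will be composed of 68 participants as minimum".

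The Abstract (Method) gives the same 68 and 34 per arm. The Allocation and blinding section fixes a 1:1 ratio, so 52 means 26 per arm. The section prints no formula for the dropout allowance. It names G*Power but neither the test chosen in it nor whether the test is one-sided or two-sided.

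**The concern.** An allowance for dropout is meant to leave the required number once the expected losses have occurred. Here 52 is the required number and 68 is presented as the figure that already allows for 30% loss. Taking 30% off 68 does not give 52. As printed, the protocol's own minimum fails at the protocol's own expected dropout, and the .80 power attached to 52 does not carry over to the sample the trial expects to keep.

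**Working it through.** **Inputs (Sample size section; allocation ratio from Allocation and blinding).** Required sample 52, or 26 per arm; dropout 30%; target 68, or 34 per arm; d = 0.4; power .80; α = .05. A two-sided test is assumed.

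**Step 1. Reproduce the stated target.** Adding 30% to the required number gives:

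- total: 52 × 1.30 = 67.6, rounded up to 68
- per arm: 26 × 1.30 = 33.8, rounded up to 34

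Both match the printed figures. The route is an inference from that match.

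**Step 2. The number needed to retain 52.** The formula is n / (1 − dropout):

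- total: 52 / 0.70 = 74.3, so 75
- equal arms: 26 / 0.70 = 37.1, so 38 per arm and 76 in total

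**Step 3. What 68 retains.**

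- 68 × 0.70 = 47.6 in total, and 34 × 0.70 = 23.8 per arm
- shortfall: 52 − 47.6 = 4.4
- largest dropout at which 68 still keeps 52: 1 − 52/68 = 23.5%

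Step 3 does not depend on Step 1. The shortfall is there however 68 was obtained.

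**Step 4. Effect on power.** The protocol does not name its test, so two designs that give 52 were used.

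- *Paired t-test*, two-sided, d = 0.4, noncentrality 0.4 × √n, n − 1 degrees of freedom.
- *Repeated-measures group-by-time interaction*, two groups, two measurements, f = d/2 = 0.2, correlation 0.5 (number of measurements and correlation assumed). Noncentrality is f² × [m / (1 − ρ)] × N = 0.04 × 4 × N, on 1 and N − 2 degrees of freedom.

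| Retained | Paired t-test | Repeated-measures interaction |
|---|---|---|
| 52 | .808 | .807 |
| 48 | .775 | .774 |
| 47 | .766 | – |
| 46 | – | .756 |

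The interaction is shown for even totals, to keep the arms equal. Both designs meet .80 at 52 and fall to about .77 at 48, a loss of 3 to 4 percentage points.

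**The case against.** Four points can be made for the protocol.

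**The figure is a minimum.** Both the Sample size section and the Abstract call 68 a minimum, so the sponsor may recruit more. That limits the harm. It does not correct the figure, because the minimum is presented as already covering 30% dropout.

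**Dropouts are not lost altogether.** The Statistical methods section plans a mixed model, and says of it that "it is conducted using all available observations". Someone who leaves between months 3 and 6 still contributes to the 3-month comparison, which is the first objective, and the protocol does not say at which time point the 30% applies. Of 68 recruits, 68 × 0.30 = 20.4 are expected to drop out, while 68 − 52 = 16 can be lost before the number falls below 52. If at least (20.4 − 16) / 20.4 = 22% of the dropouts left after month 3, 52 would still supply 3-month data. This softens the point. It does not remove it: the protocol itself enlarged 52 for dropout, so 52 is meant as the retained number, and a participant with only a baseline adds little to the 3-month contrast.

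**The 30% may not apply to both arms.** The figure is given for Internet-based interventions, and waiting-list participants have no programme to leave before month 3. With 30% lost in the intervention arm, 52 in total would remain if the waiting list lost no more than 16/34 − 0.30 = 17%. That is possible, but the protocol makes no such distinction and sets the same 34 for each arm.

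**The loss is small.** It is: 4 to 5 participants and 3 to 4 points of power. That settles the weight of the point and not whether the figures agree.

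**Conclusion.** The point holds as a minor arithmetic correction. At the protocol's expected 30% dropout, 68 recruits leave about 48 and not 52. Matching 52 retained needs 38 per arm. Power with 48 retained is about .77 under either design examined. This assumes a two-sided test, 30% loss in both arms and no contribution from dropouts; for the interaction it also assumes two measurements and a correlation of 0.5. If some dropout falls after month 3, the loss is smaller.

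Three stronger readings are tempting, and the document does not support them.

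- A reader might take it as established that the authors multiplied by 1.3. The match is exact in total and per arm, but no formula is printed, so it remains an inference.
- A reader might treat the .77 as the power of the trial's actual analysis, or replace it with the power of a plain two-group test at follow-up. Neither is the planned analysis. That is a mixed model including baseline, and its power depends on a correlation that the document does not give.
- A reader might conclude that the trial is seriously compromised by this step. A drop of 3 to 4 points against a target described as a minimum does not show that, and no analysis changes because of it.

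**What to change.** Amend the Sample size section in one of two ways, and bring the Abstract into line.

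1. Keep 34 per arm. State that 30% dropout is expected to leave about 24 per arm, and give the power for that number with the test, sidedness, number of measurements and correlation it assumes. Say at which assessment the 30% applies. The cost is a sentence or two.
2. Keep 52 as the retained number. Correct the dropout-adjusted minimum to 38 per arm, 76 in total. The cost is up to 76 − 68 = 8 more recruits, which a stated minimum already permits.
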